#### Statistical methods

Data will be analysed using the statistic software IBM SPSS Statistics 27. Descriptive analyses will be conducted after the baseline. A multivariate analysis of variance (MANOVA) with all relevant outcome parameters as specified above will be calculated in order to test the effects of the intervention on different dependent variables. Potential covariates will be included in the analysis. Therefore, if relevant covariates occur, a MANCOVA will be performed instead of the MANOVA. A covariate will be identified as such, if a demographic variable will correlate with the outcome variable or if there is a significant difference between the intervention group and the waitlist control group across this variable.

To evaluate the effects of the stress management intervention more specifically, changes in outcome variables will be analysed by two-factorial ANOVA with repeated measures and group (intervention vs. waiting control group) as a between-person effect. The core hypothesis is that perceived stress and physiological stress parameters of leaders will significantly decrease from baseline to follow-up measurements for participants in the intervention group. Thus, we will test the interaction effect of time x group for the different outcome variables. Where necessary, Bonferroni correction will be applied to avoid inflation of the type one error by multiple comparisons.

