### Handling of missing and spurious data and drop outs

We do not expect item-wise missing values as all questionnaires will be assembled digitally with notifications if items are missing. However, in the case of missing items for questionnaires the missing item score will be substituted by the mean item score of the remaining questionnaire items.

As participating leaders can withdraw from the physiological assessments, we expect some missing data for the physiological stress measures. In physiological stress assessments, measurement errors may occur. Especially for heart rate variability, which will be measured over a period of 24 h without surveillance of clinical personnel, measurement errors may occur. Thus, all data will be checked for plausibility and carefully tested against potential measurement errors. Participants with missing or spurious data will remain in the sample and will only be excluded for those analyses that involve the missing data.

As the study has a longitudinal design that extends over 1 year in time, some dropouts will be inevitable. We will, however, endeavour to retain as many participants of the original sample and will try to maximize compliance with the study’s data assessments. We accounted for some dropouts in our power analyses. Participants who drop out after t1 (the first follow-up measurement) will be included in the data analyses up to this point in time. An intention-to-treat analysis will be conducted to evaluate whether the sub-sample of dropouts significantly differs from the adherent sample.

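### The planned intention-to-treat analysis is really an attrition check, and the named three-time-point ANOVA/MANOVA estimates the effect from complete cases only

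*Protocol article*

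**What the plan says.** Under *Handling of missing and spurious data and drop outs*, intention-to-treat appears once, with this purpose: "An intention-to-treat analysis will be conducted to evaluate whether the sub-sample of dropouts significantly differs from the adherent sample".

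The same section gives three rules for incomplete data:

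- For missing or spurious measurements: "Participants with missing or spurious data will remain in the sample and will only be excluded for those analyses that involve the missing data".
- For later dropout: "Participants who drop out after t1 (the first follow-up measurement) will be included in the data analyses up to this point in time".
- For single missing items: "the missing item score will be substituted by the mean item score of the remaining questionnaire items". This is the only imputation stated.

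Under *Statistical methods*, a MANOVA on all relevant outcome parameters comes first. Then "changes in outcome variables will be analysed by two-factorial ANOVA with repeated measures and group (intervention vs. waiting control group) as a between-person effect", and for the core hypothesis "we will test the interaction effect of time x group for the different outcome variables". *Trial design* fixes the time factor at baseline, 6 months and 12 months. *Population and sample size* requires 158 participants and raises this to 200 for a 21% failure rate that covers both loss to follow-up and missing values.

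**The concern.** Intention-to-treat describes who is in the treatment contrast: everyone randomised, in the group to which they were allocated. Asking whether dropouts resemble adherers is useful, but it estimates no treatment effect. A reader who sees the term would assume that the effect estimate keeps the comparison made by randomisation, and nothing in the article provides for that.

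The named method makes this matter. A classical repeated-measures ANOVA or MANOVA needs a full set of values for each person. Together with the exclusion rule, that makes the time-by-group test a complete-case test. If leaders who respond poorly leave one arm more readily than the other, those who remain are no longer comparable. This is credible here: participants cannot be blinded, the control group waits for its training, and the protocol expects high loss to follow-up.

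**Working it through.** **1. The protocol's own figure.** Inputs from *Population and sample size*: f = 0.25, α = 0.05, power 0.80, 2 groups, 3 times. For the time-by-group interaction in a repeated-measures MANOVA, take λ = f²·N with 2 and N − 3 degrees of freedom. At N = 158, λ = 0.0625 × 158 = 9.875 and power is 0.802, so 158 reproduces. Inflation: 158 / (1 − 0.21) = 200, which also reproduces.

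**2. What this implies for the analysis set.** 200 × 0.79 = 158 analysed and 200 × 0.21 = 42 not analysed. The sample size is thus built on a test that leaves out the 21% lost or missing. If all 200 were fully informative, power at f = 0.25 would be 0.89. That is an upper bound, because a model using partial records recovers only part of the lost information.

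**3. The T1 rule beside the ANOVA.** A leader lost after T1 has values at T0 and T1 only. The dropout rule includes this leader up to T1. The three-level ANOVA needs T2 and so excludes the leader, and no separate T0–T1 analysis is named. The two statements are not reconciled.

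**4. The joint MANOVA beside the per-outcome ANOVAs.** The MANOVA takes all outcomes together, so one missing heart rate variability, hair or saliva value removes a leader from it. The ANOVAs run outcome by outcome, so a failed recording does not remove that leader from the ANOVA of the stress reactivity scale or the HADS.

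**5. Does complete-case analysis bias the estimate?** The protocol gives no dropout by arm, so this rests on assumptions: SD 1, correlation 0.6 between all times, 21% missing at T2, all dropout after T1. The estimand is the group difference in T0–T2 change.

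| Dropout mechanism | Complete cases, true effect −0.30 | Complete cases, true effect 0 |
|---|---|---|
| Unrelated to outcome | −0.30 | 0.00 |
| Poor T0–T1 change, both arms | −0.29 | 0.00 |
| Poor T0–T1 change, intervention arm only | −0.37 | −0.08 |
| Opposite directions in the two arms | −0.45 | −0.15 |

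When dropout depended on the T1 level rather than on the change, complete cases showed no bias under this correlation structure, even with mechanisms that differed by arm. An estimator using all T0 and T1 values under missing-at-random came within 0.005 of the true value in every scenario above.

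**6. Item rule.** *Questionnaires* (leaders) describes the ERI as having exertion and reward items on five points and over-commitment items on four, and the HADS as seven anxiety and seven depression items. If the mean is taken over the whole questionnaire, as the wording allows, it mixes response ranges in the first and constructs in the second.

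**The case against.** The strongest reply is that an article condenses a fuller plan and may leave missing-data methods to it. That would answer an omission. Here the article gives the term a purpose that is not intention-to-treat and names a method and an exclusion rule that together produce complete cases.

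Second, the loss is already budgeted: 158 is what remains after the 21%. This stands for power, but it does not protect the estimate. A reader might infer that the MANOVA is badly underpowered because many physiological values could fail. The documents do not support a figure: they give no loss rate per measure, losses probably cluster in leaders who decline the physiological assessments, and the sizing formula is for one outcome's interaction, not a joint test of all outcomes.

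Third, a reader might infer that the estimate is biased towards benefit by a known amount. It is not shown. The 21% includes failed measurements and is not a count of intervention-arm dropouts who gained nothing. Nor would a missing-at-random model cure that extreme case. With completers gaining 0.50 SD and 21% non-gainers all lost from the intervention arm, the true effect is 0.79 × 0.50 = 0.395. The model returns 0.50 if they leave before T1 and 0.46 if they leave after. This is why a sensitivity analysis belongs in the fix.

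Fourth, nothing excludes a leader who skips sessions but completes the assessments, so *complete* refers to assessments, not attendance.

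Fifth, the rule to include leaders up to T1 would fit a T0–T1 comparison, so the T1 data are not necessarily discarded. That stands, but no such comparison is named.

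On the items, the online forms flag gaps, so few are expected. The article describes ERI exertion and reward with one response format running towards adversity, so a claim that they are scored in opposite directions has no support.

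**Conclusion.** The concern holds in this form. The article labels an attrition check as intention-to-treat, plans no as-randomised effect estimate, and tests time by group on leaders with complete assessments, about 158 of 200 at its own loss rate. The rule for leaders lost after T1 is not reconciled with the three-time-point ANOVA. That exclusion follows from the named method and the stated rule; the article does not use the term listwise deletion.

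Bias is a risk whose size and direction are unknown. Under the stated simulation assumptions it ran from none to about 0.15 SD, and it became material only when dropout depended on T0–T1 change and the mechanism differed by arm. The joint MANOVA is the most exposed analysis; the per-outcome ANOVAs are less so. The item rule is a minor point.

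**What to change.** 1. Define intention-to-treat as all randomised leaders analysed in their allocated group.
2. For each outcome, test time by group with a likelihood-based mixed model for repeated measures on all available T0, T1 and T2 values, in place of the complete-case ANOVA/MANOVA. The named software offers this (SPSS MIXED). Multiple imputation is an acceptable alternative. Either one also makes good the promise to use data up to T1.
3. Add a sensitivity analysis for data not missing at random.
4. Rename the dropout comparison *attrition analysis*.
5. Restrict item-mean substitution to items of the same subscale.

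The cost is a little more analysis work and rewording, with no new data and no change in sample size. The main analysis would rely on missing-at-random, which is still an assumption but weaker than the one complete cases need.

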### Monitoring

*Data monitoring*. A data monitoring committee is usually formed to monitor the data for potential adverse effects the intervention has on the participants. Since the intervention has no known risk, no data monitoring committee is formed. Furthermore, no interim analysis is conducted and no stopping guidelines are formulated.

*Harms*. The intervention has a low risk of adverse effects. Therefore, no potential harm is recorded. During the intervention sessions participants are monitored by the trainers. If there are unexpected adverse effects, the present trainer takes care of the concerned participant after the training. With regard to the measurements, no risk or complications are expected from measuring blood pressure and recording HRV by using electrodes. If there is a lot of hair on the chest, it may be necessary to remove the hair. However, no permanent damage is to be expected. All experimental procedures used in the study are harmless to health. The only possible risk of becoming aware of sensitive personal data is minimized by pseudonymization and access restrictions.

*Auditing.* No auditing is planned. An ongoing process evaluation takes place within the respective study sites and in the study network as whole. Corrective action will be taken when necessary.

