## Method

### Population and sample size

#### Leaders

The target group are leaders of small and medium-sized enterprises (SMEs). We define SMEs as enterprises with up to 500 employees [50, 51] without regarding the annual sales. Leaders of all genders aged between 18 and 65 years are allowed to participate as long as they are not about to retire within the next year. A sample size of *n* = 100 participants in the intervention group and *n* = 100 participants in the waiting control group is planned (*N* = 200 participants).

The sample size calculation was performed using G*Power3.1. Based on a 2 × 3-mixed design (factor 1 (group): intervention or waiting control group; factor 2 (point in time): baseline, 6 months and 12 months later) the required sample size for a MANOVA with measurement repetition was estimated using the following predefined parameters: mean effect size f = .25 (Ω = 0.06), α-error = .05, test strength 1-β = .80. This results in a required sample size of *n* = 158 participants (*n* = 59 per group). The calculation of the required sample size was based on the procedure proposed by Prajapati et al. (2010) to calculate the required sample sizes for all possible effects (within, between, interaction) of the present design and to use the largest calculated sample size. Due to the high effort of the outcome criteria to be collected (e.g., saliva samples, 24-h heart rate variability) a high lost-to-follow-up as well as numerous missing values can be expected. We therefore calculate with a total failure rate of 21% (lost-to-follow-up and due to missing values), resulting in a required sample size of *N* = 200 (*n* = 100 per group at T_0_).

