**Methods: Monitoring**			
Data monitoring	21a	Composition of data monitoring committee (DMC); summary of its role and reporting structure; statement of whether it is independent from the sponsor and competing interests; and reference to where further details about its charter can be found, if not in the protocol. Alternatively, an explanation of why a DMC is not needed	10
	21b	Description of any interim analyses and stopping guidelines, including who will have access to these interim results and make the final decision to terminate the trial	10
Harms	22	Plans for collecting, assessing, reporting, and managing solicited and spontaneously reported adverse events and other unintended effects of trial interventions or trial conduct	10
Auditing	23	Frequency and procedures for auditing trial conduct, if any, and whether the process will be independent from investigators and the sponsor	10

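### The Harms paragraph rules out recording adverse effects while foreseeing that trainers may have to deal with them, so the trial could report no adverse-event count

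*Protocol article*

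**What the plan says.** All the relevant rules are in the Monitoring section of the protocol article.

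- **Data monitoring.** The committee is waived on the ground of absent risk: "Since the intervention has no known risk, no data monitoring committee is formed".
- **Harms, premise and rule.** The paragraph opens with "The intervention has a low risk of adverse effects" and concludes "Therefore, no potential harm is recorded".
- **Harms, observation and response.** "During the intervention sessions participants are monitored by the trainers", and "If there are unexpected adverse effects, the present trainer takes care of the concerned participant after the training".
- **Harms, measurements.** After the text on blood pressure and heart rate variability recording comes "All experimental procedures used in the study are harmless to health". The paragraph then names disclosure of sensitive personal data as the sole risk.

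In the Appendix, item 22 of the SPIRIT checklist is described as "Plans for collecting, assessing, reporting, and managing solicited and spontaneously reported adverse events and other unintended effects of trial interventions or trial conduct" and is given as addressed on page 10. No other section of the article sets up collection of adverse effects.

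**The concern.** Low risk is a reason for light recording. It is not a reason for none. The protocol already provides an observer (the trainers) and a response (care after the session). What it excludes is the step in between that would turn an observed event into trial data.

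This is a stated decision, so it cannot be excused as detail that a condensed article leaves to a fuller protocol or an analysis plan.

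At stake is what the trial can say about unwanted effects when it reports. The Dissemination policy section addresses results to policy makers, health insurers and the SME sector, and the Background argues for making such trainings widely available. The Background also describes the training as including psychodynamic elements, and the Intervention section lists, provisionally, a module on emotional conflict and a separate one on participants' own cases. The documents give no evidence that these cause harm. Under the present rule the trial could not report a number of adverse events, not even a supported zero.

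**Working it through.** The protocol states no figure on harms, so there is none to reproduce. The check is a reading of the text, followed by a calculation for scale only.

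**1. Does the text provide for documentation anywhere?**

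| Step | Provided for? | Where |
|---|---|---|
| Someone observes participants | Yes, trainers, during sessions | Monitoring, Harms |
| Someone responds to an event | Yes, the trainer present | Monitoring, Harms |
| The event is documented | No, ruled out | Monitoring, Harms |
| Events are counted and reported | No | Not found in any section |
| Checklist item on collecting and reporting events | Given a page number | Appendix, item 22 |

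**2. Do other outcomes fill the gap?** Under Outcome variables (Leaders), both arms complete HADS, EQ-5D-5L and the health-care use inventory at T0, T1 and T2. Sick days are also recorded. Under Statistical methods, outcomes are analysed by MANOVA or MANCOVA and by repeated-measures ANOVA of the time-by-group interaction. These compare means. A mean can improve while some leaders get worse, and no count of leaders who worsen is stated. The other outcomes therefore give a group-level signal and no event-level record.

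**3. What would recording allow?** Inputs: 100 leaders per arm and a total failure rate of 21% (Population and sample size, Leaders), so 100 × (1 − 0.21) = 79. If zero events are recorded among n fully observed leaders, the exact one-sided 95% upper bound on the true rate is 1 − 0.05^(1/n), and the upper limit of a two-sided 95% interval is 1 − 0.025^(1/n).

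| n | One-sided | Two-sided |
|---|---|---|
| 79 (after 21% loss) | 3.72% | 4.56% |
| 100 (intervention arm) | 2.95% | 3.62% |
| 200 (if the waiting group's later training were also logged) | 1.49% | 1.83% |

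The chance of seeing at least one event is 1 − (1 − p)^n. The documents give no event rate, so the values of p are assumptions.

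| Assumed rate p | n = 79 | n = 100 |
|---|---|---|
| 1% | 54.8% | 63.4% |
| 2% | 79.7% | 86.7% |
| 5% | 98.3% | 99.4% |

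With no recording, neither an estimate nor a bound can be given at any n.

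**The case against.** The strongest reply is proportionality. This is a training of one and a half days with two 180-minute boosters, for working leaders, with ethics approval. No safety objective is listed under Aims and objectives, so no safety conclusion is promised. Light harm monitoring is defensible here, and nothing in this point calls for a data monitoring committee. But that argument supports a short log. It does not support a rule against keeping one.

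Four further objections limit how far the point can be taken.

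- **A reader might infer that the protocol declares the training harmless.** It does not. That sentence refers to experimental procedures and follows the text on measurements. For the training, the article speaks of low risk or no known risk.
- **A reader might infer that trainers will meet adverse effects and that the information is thrown away.** The text on trainer care is conditional, and it nowhere speaks of discarding anything. The rule is also loosely worded: it could mean that no harm is noted in advance. The non-collection reading is at least as natural, and the text offers nothing to rule it out.
- **A reader might infer that the trial ends with no information on harm.** That is too strong, because the outcomes in step 2 could show worsening at group level.
- **The risk statements are not a strict contradiction.** Having no identified risk is compatible with a small residual chance of something unexpected, and the sentence on data disclosure may be meant for the measurements only. A checklist page number also shows only where an item is discussed. What stands is that the statements are hard to read together and that the cited page answers item 22 by declining to record.

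The zero-event bounds are generic: they would apply to any trial of this size with complete ascertainment, and they measure no error in this protocol.

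**Conclusion.** The point holds in a limited form. The protocol fixes a rule that excludes documentation of adverse effects, in the same paragraph that foresees trainers having to care for affected participants. As written, the trial could give no adverse-event count, and no analysis of individual worsening is stated to stand in for one.

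The documents do not support the stronger conclusions that the trial claims the training is safe, that harm is expected, or that no data bearing on harm will exist. The efficacy and cost-effectiveness analyses are unaffected.

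Its size can only be illustrated: a one-sided bound of about 3% to 3.7% would be available from zero logged events in 100 to 79 leaders, against no bound under the present rule. This assumes that every event among those leaders is captured. Ascertainment through trainers alone would be less complete than that, since they observe participants only in sessions.

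**What to change.** 1. **Replace the recording rule.** State that adverse effects noticed by trainers or study staff, or reported by participants, are logged and reported by arm. This concerns documentation only; how an affected participant is looked after is not at issue.
2. **Add one table.** Report the share of leaders in each arm whose HADS anxiety or depression score worsens from baseline by a margin fixed before the data are seen, with denominators. The scores are already collected at T0, T1 and T2. The documents give no margin, so the sponsor must choose one.
3. **Reconcile the text.** Bring the statements on no known risk, low risk and the sole possible risk into line, say which apply to the training and which to the measurements, and make the item 22 entry match what is done.

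An open question on unwanted effects at T1 and T2 is optional. Participants are unblinded and the waiting group is untrained until after T2, so the answers would be hard to compare between arms.

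The cost is a short log and one extra table. One limit should be stated in the protocol: before T2, trainer-observed events can arise only in the trained arm, so those counts are descriptive and not a between-arm comparison. The HADS table does allow one.
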